## Abstract

**Background:**

Growing evidence suggests that surgical treatment of ICH may be beneficial, particularly when performed early, with minimally invasive procedures, and in patients with lobar ICH. However, the available evidence is limited by risk of bias, heterogeneity and imprecision, and data supporting a beneficial effect in deep ICH is limited.

**Aim:**

To determine whether early minimally invasive endoscopy-guided surgery in addition to standard medical management improves functional outcome in patients with spontaneous supratentorial ICH, compared with standard medical management alone.

**Study design:**

The Dutch ICH Surgery Trial (DIST) is a multicentre, prospective, randomised trial with open-label treatment and blinded end-point assessment conducted in 11 neurosurgical centres in the Netherlands. Six hundred adult patients with spontaneous supratentorial ICH with a haematoma volume ≥ 10 mL and an NIHSS score ≥2 will be enrolled. Patients will be randomised (1:1) to minimally invasive endoscopy-guided surgery within 8 hours of symptom onset in addition to standard medical management, or to standard medical management alone.

**Study endpoints:**

The primary outcome is the mRS score at 180 days. Secondary outcomes include the mRS at 90 and 365 days, safety and technical efficacy outcomes, quality-of-life measures and health economic evaluations up to 365 days. In addition, DIST will investigate blood and imaging biomarkers of secondary brain injury.

**Summary:**

Dutch ICH Surgery Trial assesses the efficacy of early endoscopy-guided surgery for patients with supratentorial ICH. Recruitment started in November 2022; as of October 2025, 235 participants have been enrolled. Completion of recruitment is expected in 2027.

**Trial registration:**

ClinicalTrials.gov NCT05460793.

## Introduction

Intracerebral haemorrhage accounts for approximately 28% of all strokes worldwide and carries devastating consequences.^1^ One-month case fatality is 36%, and less than one-third of patients have a good functional outcome.^2^ Currently, treatments of proven benefit are limited to stroke unit care^3^ and early treatment of hypertension,^4^ preferably as part of an acute care bundle combining blood pressure lowering with anticoagulation reversal, access to critical care and neurosurgery in selected patients.^5-7^

The role of surgery in the treatment of ICH remains uncertain.^8^ The randomised trials STICH and STICH II showed no beneficial effect of surgical clot removal, mostly performed via craniotomy.^9^^,^^10^ However, in both studies, surgery was performed late after symptom onset (median times 30 and 26 hours) and over 20% of patients assigned to initial conservative treatment underwent surgery after secondary deterioration. SWITCH provided weak evidence suggesting that decompressive craniectomy without haematoma evacuation may benefit patients with severe deep ICH, but at the expense of severe disability among survivors.^11^ Regarding minimally invasive techniques, MISTIE III showed that catheter-based ICH aspiration with local administration of alteplase, started at a median of 59 hours after symptom onset, failed to improve functional outcome.^12^ More recently, ENRICH demonstrated that minimally invasive trans-sulcal parafascicular haematoma evacuation, performed at a median of 17 hours after last known well, improved functional outcome when compared to standard medical management.^13^ However, as only 2.6% of screened patients were included, and the effect was mainly attributable to patients with lobar ICH, more data are needed to confirm whether these results are robust and generalisable. The recently published MIND trial was terminated early following the ENRICH results and consequently lacked power to detect differences in functional outcome.^14^ Nevertheless, MIND demonstrated that minimally invasive endoscopy-guided surgery can effectively reduce ICH volume, with no apparent difference in efficacy between lobar and deep ICH, thereby supporting further randomised evaluation of this technique.

Surgical haematoma evacuation aims to alleviate the direct mass effect caused by the haematoma and to reduce intracranial pressure. In addition, haematoma evacuation may prevent secondary deterioration due to haematoma growth and attenuate secondary injury caused by blood degradation products.^15^ As haematoma expansion mostly occurs within the first hours after ICH,^16^ and the secondary injury cascade starts within hours after onset,^17^ early surgical intervention may offer advantages over later treatment.^18^ Moreover, minimally invasive techniques may mitigate the risks associated with open surgery, which may be particularly important for deep ICH. In the Dutch ICH Surgery Trial (DIST) pilot study, we demonstrated that minimally invasive endoscopy-guided surgery, performed within 8 hours of symptom onset, was safe, feasible and effectively reduced haematoma volume.^19^ Safety, logistical and technical feasibility have also been demonstrated in another study.^20^

The DIST aims to assess whether early minimally invasive endoscopy-guided surgery, in addition to standard medical management, improves functional outcome after spontaneous supratentorial ICH when compared to standard medical management alone.

**Table 1 TB1:** Inclusion and exclusion criteria

**Inclusion criteria**	**Exclusion criteria**
Age ≥ 18 years NIHSS score ≥ 2 Supratentorial non-traumatic ICH confirmed by CT, without a confirmed causative vascular lesion on admission CTA (eg, aneurysm, arteriovenous malformation, dural arteriovenous fistula, cerebral venous sinus thrombosis), or other known underlying lesion (eg, tumour, cavernoma) Haematoma volume ≥ 10 mL Intervention can be started ≤ 8 hours of symptom onset Written informed consent (deferred)	Pre-stroke mRS score ≥ 3 ICH-GS score ≥ 11^31^ Haemorrhage due to haemorrhagic transformation of an infarct Untreated coagulation abnormalities, including INR > 1.3, treatment with heparin and treatment with factor Xa inhibitors. Patients on vitamin K antagonists can be included after correction of the INR, and patients on dabigatran can be included after reversal with idarucizumab Moribund (eg, coning, bilateral dilated unresponsive pupils), or progressively deteriorating clinical course with imminent death Pregnancy DIST-INFLAME substudy: patients who use immunosuppressive or immune-modulating medication

Abbreviations: ICH-GS = Intracerebral Haemorrhage-Grading Scale; INR = international normalised ratio.

## Methods

### Study design

Dutch ICH Surgery Trial (www.dutch-ich.nl) is a multicentre, prospective, randomised (1:1) controlled trial with open-label treatment and blinded endpoint assessment, investigating whether minimally invasive endoscopy-guided surgery within 8 hours of symptom onset, in addition to standard medical management, improves functional outcome at 6 months, in comparison with standard medical management alone. The trial will be conducted in 11 neurosurgical centres in the Netherlands (Supplemental material).

In parallel, DIST-ABC (A Budget Impact and Cost-effectiveness analysis) will evaluate the cost-effectiveness and budget-impact of minimally invasive endoscopy-guided surgery from a healthcare system perspective.

The DIST-INFLAME substudy will: (1) assess whether patients treated with minimally invasive surgery develop less perihaematomal oedema than patients treated with standard medical management alone, (2) assess whether this effect is modified by the CTP permeability surface-area product around the ICH at baseline, and (3) compare immune profiles over time in venous blood between surgically treated patients and patients treated with standard medical management alone.

DIST is embedded within the Collaboration for New Treatments of Acute Stroke (CONTRAST 2.0) consortium (www.contrast-consortium.nl), which supports multicentre stroke research in the Netherlands. The study will be conducted according to the principles of the Declaration of Helsinki and in accordance with the Medical Research Involving Human Subjects Act Wet medisch-wetenschappelijk onderzoek met mensen (WMO). The study has been approved by the Erasmus MC medical ethics review committee (NL80112.078.22) and is registered on ClinicalTrials.gov (NCT05460793).

### Patient population

Adults with a spontaneous, supratentorial ICH presenting to 1 of 11 neurosurgical centres, or referred to these centres by regional hospitals, can be enrolled. Inclusion and exclusion criteria are listed in Table 1.

### Randomisation

Eligible patients will be randomised by local site personnel via a secure web-based internet system. Patients will be allocated in a 1:1 ratio to either minimally invasive endoscopy-guided surgery in addition to standard medical management (intervention group), or to standard medical management alone (control group), using permuted blocks with random block sizes of 10 or 20 stratified by neurosurgical centre. It will not be possible to view the treatment allocation before the patient is randomised. Due to the nature of the intervention, both patient and local site personnel cannot be blinded for the assigned treatment.

### Deferred consent procedure

Patients will be enrolled using a deferred consent procedure in accordance with the Medical Research Involving Human Subjects Act (WMO).^21^ Written informed consent to continue participation in the study will be obtained from the patient or their representative by trained research personnel, as early as deemed appropriate and reasonable after randomisation (control group) or intervention (intervention group). In patients allocated to the intervention group, we will ask the patient or their representative for consent for the surgical treatment according to common clinical practice for any procedure. Patients who have indicated, as part of advanced care planning, that they do not want to undergo any surgical treatment will not be enrolled. When a representative has provided consent and the patient regains decision-making capacity, we will ask the patient for written consent at that time. If a patient has died before deferred consent has been obtained, the legal representative will be informed about trial participation. Patients or representatives who do not consent will be asked for permission to use routinely collected data and materials. If patients or their representatives object to the use of their data, their data will be registered in an anonymized registry to obtain data on in-hospital rebleeding occurrence and in-hospital mortality for the purpose of safety analyses. All other study information will be completely erased from the patient’s study record.

### Intervention

Patients allocated to the intervention group will undergo minimally invasive endoscopy-guided surgery within 8 hours of symptom onset. The trial allows the use of any Conformité Européenne (CE)-marked minimally invasive neuronavigation integrated endoscopy-guided device; currently, this includes only the Artemis™ Neuro Evacuation Device (Penumbra, Inc.). With the neuronavigation software available at the neurosurgical centre, a trajectory is selected that is considered technically feasible, safe and allows access to the longest axis of the haematoma. Intracranial access is obtained via a burr hole, after which a peel-away sheath is introduced to facilitate safe passage of the endoscope during the procedure. Surgery is performed by credentialed neurosurgeons in accordance with the DIST surgical protocol. Credentialing includes successful participation in the DIST pilot study or completion of a dedicated qualification process. The DIST surgical protocol and credentialing procedure are outlined in the Supplemental material.

Both patients in the intervention and control groups will receive standard medical management according to the Dutch^22^ and European Stroke Organisation^7^^,^^23^ guidelines for the management of spontaneous ICH.

### Study procedures

In addition to the study intervention, patients will undergo study assessments at day 0 (admission), day 1 (±6 hours), day 3 (±12 hours), day 6 (±1 day, or discharge if earlier) and during follow-up at days 90, 180 and 365 (±14 days) (Figure 1).

**Figure 1 f1:**
[figure not shown]
SPIRIT figure of Dutch ICH Surgery Trial (DIST). Abbreviations: EQ-5D-5L = EuroQol five dimensions-five levels; GCS = Glasgow coma scale; NCCT = non-contrast computed tomography; SAE = serious adverse event; SS-QoL = Stroke Specific Quality of Life.

#### Clinical data

Baseline characteristics will be assessed by treating physicians upon presentation to the emergency department. Vital signs will be collected at 1, 6, 12 and 24 hours post-admission, day 3 (±12 hours; DIST-INFLAME only) and day 6 (±1 day). NIHSS and EuroQol five-dimension five-level (EQ-5D-5L) assessments will be performed at day 6 (±1 day). Details of the surgical intervention, treatment limitations, interventions, diagnoses and medication use will also be recorded during hospitalisation.

#### Blood sampling

We will collect blood at baseline obtained as part of routine clinical practice. We will draw additional blood samples (serum, plasma EDTA, whole blood EDTA, citrate and PAXgene tubes) in all patients at baseline, and in patients in the DIST-INFLAME substudy at day 3 (±12 hours) and day 6 (±1 day).

#### Neuroimaging

Patients will undergo a baseline brain non-contrast CT (NCCT) and CTA. To assess eligibility for the study, haematoma volume will be calculated using the ABC/2 formula^24^ or volumetric 3D software upon presentation at the emergency department. In patients in the DIST-INFLAME substudy, a baseline CTP will be performed according to a prespecified protocol. An immediate postoperative NCCT will be performed to assess ICH evacuation. In addition, all patients will undergo NCCT at 24 hours (±6 hours) and day 6 (±1 day). The CT acquisition protocol requirements are described in the Supplemental material.

#### Follow-up assessment

Trained research personnel, unaware of treatment allocation, will assess the mRS, Barthel Index, EQ-5D-5L and Stroke-Specific Quality of Life (SS-QoL) scale using standardised reports via telephone interviews at 90, 180 and 365 days. Similarly, home time and patient location will be assessed at these time points. Health economic evaluations will be evaluated using questionnaires based on the iMTA Medical Consumption Questionnaire (iMCQ), the iMTA Productivity Cost Questionnaire (iPCQ), and the iMTA Valuation of Informal Care Questionnaire (iVICQ).

#### Deferred consent evaluation

In a sample of 100 patients, we will evaluate the acceptability of the deferred procedure by means of a pre-piloted questionnaire between 90 and 180 days. In addition, a subsample of patients will be invited to an in-depth interview.

### Study outcomes

The primary outcome is the mRS score at 180 days (±14 days).^25^ The mRS is a 7-category ordinal disability scale with scores ranging from 0 (no symptoms at all) to 6 (death). Secondary, safety, technical efficacy and DIST-INFLAME substudy outcomes are listed in Table 2.

**Table 2 TB2:** Study outcomes in Dutch ICH Surgery Trial (DIST)

Primary endpoint mRS score at 180 days (ordinal distribution) Secondary endpoints mRS score at 90 and 365 days (ordinal distribution) Good outcome (mRS score 0-2) at 90, 180 and 365 days Favourable outcome (mRS score 0-3) at 90, 180 and 365 days All other possible dichotomisations of the mRS score at 90, 180 and 365 days NIHSS score at 6 days (or discharge if earlier) Death at 90, 180 and 365 days Barthel Index score at 90, 180 and 365 days Quality of life assessed with the EQ-5D-5L at 6 days (or discharge if earlier), and 90, 180 and 365 days Quality of life assessed with the SS-QoL at 90, 180 and 365 days Resource use assessed with the iMCQ and iPCQ at 90, 180 and 365 days Burden for the caregiver assessed with the iVICQ at 90, 180 and 365 days Home time at 90, 180 and 365 days Patient location over the first 90, 180 and 365 days Safety outcomes Death within 24 hours Procedure-related complications within 7 days Case-fatality at 7 and 30 days Technical efficacy outcomes Percentage volume reduction based on baseline NCCT and NCCT at 24 hours Percentage participants with haematoma volume reduction ≥70% Percentage participants with haematoma volume reduction ≥80% Percentage participants with remaining haematoma volume ≤ 10 mL Percentage participants with remaining haematoma volume ≤ 15 mL Percentage participants with conversion to craniotomy DIST-INFLAME substudy outcomes Perihaematomal oedema assessed on NCCT at 6 days (or discharge if earlier) mRS score at 180 days Immune and metabolomic profiles in venous blood assessed at 3 and 6 days (or discharge if earlier)

Abbreviations: EQ-5D-5L = EuroQol five dimensions-five levels; iMCQ = iMTA Medical Consumption Questionnaire; iPCQ = iMTA Productivity Cost Questionnaire; iVICQ = iMTA Valuation of Informal Care Questionnaire; NCCT = non-contrast computed tomography; SS-QoL = Stroke Specific Quality of Life.

Adjudication of the mRS score will be performed by an outcome assessment committee blinded to treatment allocation (Supplemental material). Their assessments will be based on the standardised reports of the follow-up interviews by trained research personnel. Information on follow-up assessments in the main study database will only be visible by outcome assessors and the independent, unblinded statistician of the data safety monitoring board (DSMB).

Imaging will be assessed by experienced neuroradiologists of the imaging assessment committee (Supplemental material). Baseline imaging will be evaluated blinded for baseline characteristics, treatment allocation and outcome measures. Follow-up imaging will be evaluated blinded for baseline characteristics, outcome measures and for the results of baseline imaging.

### Data and safety reporting

All serious adverse events (SAEs) occurring until the end of follow-up will be centrally assessed by the SAE adjudication committee (Supplemental material). Study safety will be monitored by an independent DSMB consisting of a neurologist, a neurosurgeon and an independent methodologist/statistician (Supplemental material). Interim safety and efficacy analyses will be performed at least annually or after completion of 30-day follow-up of the first 50 and subsequent 100, 250 and 400 enrolled patients. Results of interim analyses will be provided to the DSMB by an independent, unblinded statistician in strict confidence, along with any other analyses the DSMB may request. The steering committee will remain blinded to the results of interim analyses of efficacy and safety.

### Statistical analysis

The primary analyses will be performed according to the intention-to-treat principle. Baseline data by treatment allocation will be reported with standard statistical procedures. Missing values for baseline characteristics and outcomes will be reported. For the analyses, missing baseline characteristics and outcomes will be imputed using multiple imputation.

The primary effect parameter will be reported as a common odds ratio, estimated with ordinal logistic regression, which represents the shift across the 7-category mRS measured at 180 days. The treatment effect estimate will be adjusted for neurosurgical centre and known prognostic variables: age, pre-stroke mRS, time from symptom onset to randomisation, systolic blood pressure on admission, stroke severity (NIHSS), ICH volume, presence of intraventricular haemorrhage and antiplatelet or oral anticoagulant use immediately before stroke onset. Adjusted and unadjusted estimates with corresponding 95% CIs will be reported. The adjusted analysis with multiple imputation will be considered the primary analysis. In addition, we will perform a per-protocol and as-treated analysis.

Secondary effect parameters will be analysed using linear, logistic or ordinal regression analyses as appropriate, applying the same adjustment variables as for the primary outcome.

The effect of the intervention on the mRS will be analysed in pre-specified subgroups determined by the following variables: tertiles of age; sex; location of ICH (deep vs lobar); tertiles of systolic blood pressure at baseline; tertiles of NIHSS at baseline; tertiles of ICH volume; tertiles of time from symptom onset to randomisation; presence of CTA spot sign and prior use of antiplatelet agents or oral anticoagulants.

For the cost-effectiveness analysis, costs and quality-adjusted life years will be calculated in both groups over the 12-month follow-up period. We will perform a model-based economic evaluation to estimate the lifetime cost-effectiveness of the intervention.

Further details will be provided in a separate statistical analysis plan.

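### Adding ICH location (deep vs lobar) to the primary adjustment set would be a nearly free improvement; leaving it out is not an error

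*Protocol article*

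**What the plan says.** Under Statistical analysis, the protocol article lists the adjustment variables of the primary model: "The treatment effect estimate will be adjusted for neurosurgical centre and known prognostic variables: age, pre-stroke mRS, time from symptom onset to randomisation", then admission systolic blood pressure, and then "stroke severity (NIHSS), ICH volume, presence of intraventricular haemorrhage and antiplatelet or oral anticoagulant use immediately before stroke onset". The list is not worded as open-ended. The article then states: "The adjusted analysis with multiple imputation will be considered the primary analysis". Secondary outcomes use the same covariates.

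Location appears in that section only among the subgroups: "tertiles of age; sex; location of ICH (deep vs lobar); tertiles of systolic blood pressure at baseline". Under Randomisation, allocation is made "using permuted blocks with random block sizes of 10 or 20 stratified by neurosurgical centre", so location is not balanced by design.

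The Introduction says of ENRICH that "the effect was mainly attributable to patients with lobar ICH, more data are needed to confirm whether these results are robust and generalisable". The same paragraph reports that MIND found no apparent lobar/deep difference in efficacy, in a sentence about volume reduction. No section calls location a prognostic variable for the mRS.

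**The concern.** Location is prominent in the trial's rationale. The Abstract singles out lobar ICH as the setting where surgery may help and says that data in deep ICH are limited. Nine subgroup variables are listed. Six of them (age, systolic blood pressure, NIHSS, volume, onset-to-randomisation time and antithrombotic use) are also in the adjustment set. Location, sex and CTA spot sign are not, and no reason is given.

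The Sample size calculation cuts N from 800 to 600 on an assumed 25% saving from covariate adjustment, so it is fair to ask whether an available baseline variable has been left unused. If location is prognostic given the other covariates, leaving it out has three costs. A little precision is lost, the adjusted odds ratio is slightly attenuated, and a chance imbalance in location stays uncorrected in the primary estimate. A visible imbalance could also prompt a dispute over post hoc adjustment.

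**Working it through.** **1. The plan's own figure.** Inputs from Sample size calculation: control mRS 0 to 6 of 0/5/15/20/25/15/20%, common odds ratio 1.49, two-sided alpha 0.05, power 90%.

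- Proportional-odds (Whitehead) formula: N = 12(z_α + z_β)² / [ln(OR)² (1 − Σp̄³)], where p̄ is the mean of the two arms' category probabilities.
- The treated distribution is 0/7.27/19.87/22.69/23.62/12.18/14.37%, so Σp̄³ = 0.0372.
- N = 12 × 10.507 / (0.1590 × 0.9628) = 824, against 800 stated (2.9% apart).
- Power at N = 800 is 89.2% by formula and by a 20,000-run simulation.
- 800 × 0.75 = 600.
- Unadjusted power at N = 600 is about 79%, so the 90% target does rest on covariate adjustment in general.

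**2. Chance imbalance.** Assumed 40% lobar (the documents give no share), 300 per arm.

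- SD of the between-arm difference = √(2 × 0.40 × 0.60 / 300) = 0.040, or 4.0 percentage points.
- Difference of at least 5 points: z = 1.25, two-sided probability about 21%. At least 8 points: z = 2.0, about 5%.
- With an assumed conditional location odds ratio of 2.0, an 8-point imbalance shifts the log odds ratio by 0.08 × ln 2 = 0.055. That is 0.055 / ln 1.49 = 0.055 / 0.399 = 14% of the planned effect.
- The standard error at 90% power is about 0.399 / 3.24 = 0.12, so the shift is a little under half a standard error.

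**3. Power at N = 600 with and without location.** Proportional-odds fits to simulated trials (1,000 to 1,500 runs per scenario). Assumptions: 40% in one location class, location independent of the other covariates, and the other covariates summarised by one score with the stated SD on the logit scale. Each cell gives power without → with location.

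| Held at 1.49 | SD of other covariates | Location OR 1.5 | OR 2.0 | OR 3.0 |
|---|---|---|---|---|
| Unadjusted OR | 0.8 | 90.2 → 90.0 | 87.3 → 88.5 | 88.1 → 91.3 |
| Unadjusted OR | 1.1 | 90.7 → 90.9 | 90.5 → 91.0 | 92.1 → 93.9 |
| Unadjusted OR | 1.5 | 94.3 → 94.6 | 93.6 → 94.1 | 94.9 → 96.6 |
| Conditional OR | 1.1 | 77.1 → 77.7 | 75.1 → 77.3 | 75.3 → 78.7 |
| Conditional OR | 1.5 | 73.2 → 73.9 | 76.4 → 78.8 | 71.7 → 75.7 |

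With the unadjusted odds ratio held at 1.49, the gain is about nil at a location odds ratio of 1.5 (−0.2 to +0.3 points), +0.5 to +1.2 at 2.0, and +1.7 to +3.2 at 3.0. With the conditional odds ratio held at 1.49, the gains are about +0.6, +2.3 and +3.4 to +4.0. When location had no effect, the two models differed by up to 0.4 points, so differences of a few tenths are simulation noise.

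**4. Attenuation.** At SD 1.1 (first block), the mean adjusted odds ratio without and with location is 1.61 and 1.63 at a location odds ratio of 2, and 1.64 and 1.69 at 3.

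**5. Does the 25% saving need location?** At SD 1.1 with no location effect, and with the unadjusted odds ratio at 1.49, adjustment for the other covariates alone gives 91.9% power at N = 600. In this model the target is met without location.

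**The case against.** The strongest reply is that nothing here is wrong. The model is pre-specified, includes the stratification factor and eight prognostic variables, and is reported beside an unadjusted estimate. Under randomisation, omitting one covariate does not invalidate the test, and chance imbalance is already part of the sampling error. NIHSS, volume and intraventricular haemorrhage are adjusted for and may carry part of the location signal, so the independence assumption probably overstates the gain. Sex and spot sign are outside the adjustment set too. All of this stands, and it limits the point to an optional improvement.

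A reader might also infer more than the documents support:

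- **That location is the main driver of effect in earlier work.** This rests on ENRICH alone, and the article says that result needs confirmation. The MIND statement points the other way, though on volume reduction. The ENRICH remark also concerns effect modification, which the deep vs lobar subgroup analysis addresses; a main-effect term would not.
- **That the planned 25% saving depends on location.** Step 5 of the working shows that it need not.
- **That adjusting for volume without location is only partial, because volume means something different in deep and lobar haematomas.** Nothing in the article says so.
- **That location is missing from the imputation model.** The article does not specify that model and defers further details to a separate statistical analysis plan.

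The objection does not show any real cost to including the variable.

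**Conclusion.** The omission is a pre-specified choice that leaves the primary analysis valid and does not change the sample size. Adding location would still be a small, nearly free improvement: about 0 to +3 points of power at N = 600 for a location odds ratio of 1.5 to 3, or up to +4 if the conditional treatment odds ratio is held at 1.49. It would also correct an imbalance whose SD is about 4 points.

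These sizes rest on an assumed 40% lobar share, an assumed prognostic odds ratio, and independence from the other covariates; none of the three is given in the documents. That location is absent from the list and from the strata is certain. How much it matters is not, and at a location odds ratio of 1.5 the power gain is about nil. That location will be recorded for all patients is inferred from the subgroup list and the baseline CT and CTA.

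**What to change.** Before unblinding, add ICH location (deep vs lobar, defined as for the subgroup analysis) to the covariates of the primary model and of the secondary models that share them. In the statistical analysis plan, make sure the imputation model includes it. If the trial team prefers to leave it out, one sentence giving the reason would do.

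The cost is one degree of freedom, a wording change and no new data. The article expects recruitment to run to July 2027 and keeps the steering committee blinded to interim results, so the change can be made without knowledge of outcomes by arm.
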